### Sample size {14}

Our hypothesis is that baloxavir treatment in adult, immunocompetent patients hospitalized for influenza will shorten the time to clinical improvement by at least 36 h compared to placebo. This 36-h difference was chosen as the minimal time difference considered to have a meaningful impact on clinical care. The median time to clinical improvement, in patients who received antivirals in a large clinical study, was about 4 days (97.5 h) [16]. The addition of the 36-h difference equals a time to clinical improvement of 5.5 days in the placebo group.

Two sample size calculations were performed. Sample size calculation no. 1 concerns all patients hospitalized for influenza (regardless of symptom duration at treatment administration): under the constant and proportional hazard assumption, median times to clinical improvement of 5.5 days in the placebo group and 4 days in the baloxavir group correspond to a hazard ratio of 1.375. With a follow-up period of 30 days, we calculated that a total number of 432 participants (216 per arm) would provide the trial with at least 90% power to detect such a baloxavir effect on time to clinical improvement at a two-sided significance level of 0.05.

Sample size calculation no. 2 concerns the subgroup of patients hospitalized for influenza with symptoms evolving for less than 72 h: under similar hypothesis (median times to clinical improvement of 5.5 days in the placebo group and 4 days in the baloxavir group, corresponding to a hazard ratio of 1.375 under the constant and proportional hazard assumption, and a follow-up period of 30 days), we calculated that a sample of 161 patients per arm would provide 80% power to detect a baloxavir effect in a subgroup analysis, at a two-sided significance level of 0.05. Assuming two out of three patients will present symptoms evolving for less than 72 h (ratio of 2:1), the study will need to include a total of 484 patients. With that sample size, the study will reach a power of 93% in the general population of hospitalized patients.

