**Methods:**

This is an investigator-initiated, randomized, triple-blind, placebo-controlled, superiority, multi-center trial to assess the clinical efficacy of single-dose baloxavir in decreasing time to clinical improvement in adult immunocompetent patients hospitalized with influenza. Patients (*n* = 484) with confirmed, severe infection (NEWS2 score ≥ 4) will be recruited over three influenza seasons in four large Swiss hospitals. Primary outcome: time to clinical improvement (in hours), calculated from treatment administration until NEWS2 score ≤ 2 maintained for 24 h or until hospital discharge, whichever comes first. The primary outcome is calculated in all patients independently of the duration of symptoms at treatment administration, as well as in participants treated early (<72 h) post onset of symptoms. The main secondary outcomes are the risk of serious influenza complications, length of hospitalization, and difference in viral load at D3 post-treatment administration.

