### Objectives {7}

Primary objective: To measure the clinical efficacy of single-dose baloxavir in shortening the time to clinical improvement compared to placebo in adult immunocompetent patients hospitalized for influenza irrespective of the duration of symptoms.

Co-primary objective: To measure the clinical efficacy of single-dose baloxavir in shortening the time to clinical improvement compared to placebo in the subgroup of adult immunocompetent patients hospitalized for influenza and treated less than 72 h POS. Secondary objectives: To assess baloxavir’s efficacy in decreasing the risk for and the duration of oxygen therapy related to the influenza episode, as well as its efficacy in preventing serious influenza-related complications; to measure its effects on viral-load kinetics including duration of infectiousness.

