## Statistical methods

### Statistical methods for primary and secondary outcomes {20a}

The primary outcome (time to clinical improvement) is a time to event data. The “clinical improvement-free survival” will be estimated according to the Kaplan–Meier method and compared between groups (baloxavir vs. placebo) using a Cox model. The conditional effect of baloxavir on time to clinical improvement will be estimated with the following covariates included in the model (all collected at inclusion): age, vaccine status (yes/no), NEWS2 baseline score, BMI, and study site. As recommended by the EMA, the FDA, and ICH guidelines, we prospectively planned to include key prognostic factors as covariates in the statistical models, regardless of whether they were used for stratification during randomization. The purpose of this approach is to improve the precision of the estimated treatment effects and to account for potential imbalance in important baseline characteristics, even in randomized trials. Covariates that were not considered clinically relevant or did not demonstrate prognostic value based on prior knowledge were not included to avoid overfitting and preserve model parsimony.

First intention will be to include age and NEWS2 score as continuous variables. If the log-linearity assumption does not hold, age will be categorized as ≥65 vs. <65 years, and BMI (<30 vs. ≥30 kg/m^2^), and NEWS2 score as ≤7 vs. >7. This multivariable model will be considered the primary model. The study being a superiority trial, the principal analysis will be based on the intention-to-treat (ITT) population among all patients included in the trial independently of treatment timing POS. The same analysis will be done in the subgroup of patients receiving the study treatment ≤ 72 POS.

Clinical improvement-free survival will be estimated using the Kaplan–Meier method. For hypothesis testing, a Cox proportional hazards model will be employed. The hazard ratio (HR) will be estimated from the Cox model, and two-sided 95% confidence intervals will be derived using standard errors of the log (HR), calculated from the observed Fisher information matrix. The Breslow method will be used to handle tied event times. The proportional hazards assumption will be assessed visually using log(−log[survival]) plots. In case of a violation of this assumption, a secondary analysis will be conducted by incorporating time-dependent covariates to account for non-proportional effects.

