### Methods for additional analyses (e.g., subgroup analyses) {20b}

Subgroup analysis: using the same approach as in the primary analysis, the clinical efficacy of baloxavir in decreasing time to clinical improvement compared to placebo will be assessed in the following subgroups: patients with symptoms evolving for less than 72 h at treatment administration.

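### The <72 h analysis is co-primary in {7} and sized at its own 0.05 in {14}, yet it is a follow-on subgroup analysis in {20a} and {20b}, with no rule on which test or tests must succeed

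*Protocol article*

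**What the plan says.** Objectives {7} lists a primary objective in all patients whatever their symptom duration, followed by a second objective on the same endpoint: "Co-primary objective: To measure the clinical efficacy of single-dose baloxavir in shortening the time to clinical improvement compared to placebo in the subgroup" treated before 72 h. The Abstract (Methods) likewise attaches the primary outcome to both populations: "The primary outcome is calculated in all patients independently of the duration of symptoms at treatment administration, as well as in participants treated early".

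Sample size {14} contains two calculations, each with the whole of the significance level. For all patients, 432 participants give "at least 90% power to detect such a baloxavir effect on time to clinical improvement at a two-sided significance level of 0.05". For the <72 h group, 161 per arm give "80% power to detect a baloxavir effect in a subgroup analysis, at a two-sided significance level of 0.05". With two thirds of patients assumed to fall in that group, the second calculation raises the total from 432 to 484.

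The analysis sections rank the same test lower. In {20a}, "the principal analysis will be based on the intention-to-treat (ITT) population among all patients included in the trial independently of treatment timing POS", and the analysis is then repeated in the early-treated patients. In {20b} the <72 h group appears only under additional analyses, to be examined "using the same approach as in the primary analysis".

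No section of the article gives a testing order, a division of alpha or a definition of trial success.

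**The concern.** Two tests of one endpoint in nested populations each receive a full two-sided 0.05, and the article describes one of them as both co-primary and additional. This affects what can be claimed when the two results disagree. If the overall test misses and the <72 h test is significant, {7} and {14} would let that be presented as a successful primary-level result at 5%, while {20a} and {20b} would make it a subgroup finding beneath a failed principal analysis.

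Such disagreement is plausible. The Background section presents treatment timing as an important influence on antiviral efficacy, and the Discussion part of the Abstract expects the results to shape clinical guidance either way. A rule chosen after unblinding would not be credible.

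**Working it through.** **Inputs, all from Sample size {14}:** medians of 5.5 and 4 days, hazard ratio 1.375, 30 days of follow-up, two-sided 0.05 for each test, N = 484, subgroup 2 × 161 = 322, subgroup share 2/3. Allocation is 1:1 ({8}).

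**1. Reproducing the plan's figures.** With exponential times, the 30-day event probability is 1 − exp(−30 ln2/5.5) = 0.977 on placebo and 1 − exp(−30 ln2/4) = 0.994 on baloxavir, mean 0.986. The Schoenfeld event count is 4(z₀.₉₇₅ + z_power)²/(ln 1.375)². The Freedman count replaces 4/(ln 1.375)² with (2.375/0.375)².

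| Quantity | Schoenfeld | Freedman | Plan |
|---|---|---|---|
| Events, 90% power | 415 | 422 | – |
| N, all patients, 90% power | 421 | 428 | 432 |
| Events, 80% power | 310 | 315 | – |
| Per arm, <72 h, 80% power | 158 | 160 | 161 |
| Power at N = 484 | 93.6% | 93.2% | 93% |

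The total also follows: 322 × 3/2 = 483, against 484. The agreement needs the full 0.05 in each test, so no multiplicity adjustment is hidden in the sample size.

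**2. Correlation of the two tests.** The subgroup is nested in the whole, so with similar event rates in both strata ρ = √share = √(2/3) = 0.816.

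**3. Error under the global null.** For a bivariate normal pair with this ρ, the probability that |Z₁| > 1.96 or |Z₂| > 1.96 is 0.0770. It is 0.083 at a share of 50% and 0.071 at 80%. Two independent tests would give 1 − 0.95² = 0.0975. Counting only rejections that favour baloxavir, the figure is 3.85% against a nominal 2.5%.

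By success rule:

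| Rule | Chance of a false primary claim, global null |
|---|---|
| Either test suffices | 7.7% |
| All patients first, <72 h only after a win | 5% |
| Both required | 0.05 + 0.05 − 0.077 = 2.3% |

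**4. Power under the planning assumptions.** Expected events are 484 × 0.986 = 477 and 322 × 0.986 = 317. The drifts are √(477/4) × ln 1.375 = 3.48 and √(317/4) × ln 1.375 = 2.84. With ρ = 0.816:

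- all patients: 93.6%
- <72 h: 81.0%
- both: 80.1%
- either: 93.6 + 81.0 − 80.1 = 94.5% from these rounded values, 94.4% unrounded

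**The case against.** A reader might infer that the trial's false-positive rate is 7.7%. The article does not support that as a flat statement, because nowhere does it say that a win in either population is enough. Several features point to the all-patient test as the lead: it is listed first in {7}, it is the principal analysis in {20a}, and {14} and {20b} both call the <72 h test a subgroup analysis. On that reading an all-patient win is an ordinary 5% result. Co-primary is also often used to mean that all tests must succeed, which needs no alpha split. These points stand, and they make 7.7% conditional. They do not supply a rule: being principal is not the same as being a gatekeeper, and neither reading fits all four sections.

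A reader might also infer that a both-required design would have a power the plan never quotes. That is not so. The joint power is 80.1%, and {14} quotes 80% for the subgroup. Because the populations are nested, the two figures nearly coincide.

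Finally, multiplicity detail is often left to an analysis plan, which is not shown here. Silence alone would not be a finding. But this document itself names the test co-primary, gives it a full 0.05, lets it set the total, and then ranks it as additional. An analysis plan that split alpha would also undercut the stated powers: an equal correlation-adjusted level of 0.0318 per test gives about 91% overall and 75% for <72 h.

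**Conclusion.** The point holds as an inconsistency of status with no success rule. As written, a primary claim from either population at 0.05 is not excluded. On that reading the family-wise error is about 7.7% (7.1% to 8.3% for subgroup shares of 80% to 50%). It is 5% or less under an overall-first sequence or a both-required rule.

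The 7.7% rests on the protocol's 2/3 share, similar event rates in the two strata and the global null. The share is itself due to be checked at the blinded re-estimation in {21b}, hence the range. The sample size arithmetic is sound, and 484 need not change.

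**What to change.** State one rule, in the same terms, in {7}, {14}, {20a} and {20b}, before unblinding:

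- Test all patients first at two-sided 0.05.
- Test <72 h at two-sided 0.05 as confirmatory only if the first test is significant. Otherwise report it as supportive.
- In {14}, keep 93% as the power for the overall claim and give about 80% as the power to establish both.

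Use one boundary for the subgroup in the same edit, since {20a} includes patients at exactly 72 h and the other sections do not.

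The cost is an amendment to wording, with no extra patients and no change to data collection. The downside is real: if the overall test fails, no confirmatory <72 h claim can be made, however strong that result looks.

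An unequal alpha split is not a good substitute. For example, 0.010 for all patients and 0.047 for <72 h cuts overall power to about 82%, below the 90% minimum in {14}. Because it is tuned to a 2/3 share, its error also rises to about 5.2% if the share turns out to be 50%.

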## Introduction

### Background and rationale {6a}

Each year, influenza causes a severe disease burden worldwide. Every winter in Switzerland, several thousands of patients require hospitalization due to complicated influenza, with hundreds of deaths [1]. Treatment strategies contributing to a shorter hospital stay as well as to a lower risk of complications have major public health importance.

In addition, due to its immense capacity to evolve, influenza is one of the leading causes of human pandemics of respiratory origin [2]. The avian influenza A(H5N1) strains causing the epizootic ongoing since 2020 are not yet adapted to humans. However, each new spillover increases the risk of mutations allowing adaptation to the mammalian host [3]. Determining the best possible use of antiviral treatment resources will be crucial in case of a new pandemic.

The most frequently used antiviral drugs to treat influenza in hospitalized patients are neuraminidase inhibitors (NAI) including oseltamivir and the cap-dependent endonuclease inhibitor baloxavir marboxil (baloxavir from thereof). For uncomplicated cases in high-risk outpatients, a 16-to-25-h reduction in symptom duration was observed when oseltamivir was administered within 48 h post onset of symptoms (POS) [4–6].

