### Plans to promote participant retention and complete follow-up {18b}

Subjects who withdraw or are withdrawn from the study prior to IMP administration will be replaced. No follow-up of these subjects will be performed, and no data will be analyzed. Subjects withdrawing or withdrawn after randomization and IMP administration will not be replaced. Data and samples collected before withdrawal will be analyzed. The reason for study discontinuation or deviation will be recorded in a specific section of the e-CRF.

Patients who drop out will be right censored at the time of withdrawal, with reasons for withdrawal documented. For deceased patients, clinical improvement will be considered as having never occurred until the end of follow-up: those patients will be right censored at 30 days.

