#### Definition of relevant intercurrent events

The estimand of interest targets the effect of treatment on the time to clinical improvement within 30 days of randomization. The variable is defined as the time (in days) from randomization to clinical improvement, with a maximum follow-up of 30 days. Death before improvement is considered an intercurrent event and will be handled using a composite strategy, whereby death is interpreted as a failure to improve. In this case, the time to improvement will be right censored at day 30. Other intercurrent events are considered irrelevant to the definition of the treatment effect and will be addressed using a treatment policy strategy, meaning that patients will be analyzed according to their randomized treatment regardless of these events.

The treatment effect will be summarized by the adjusted hazard ratio with corresponding 95% confidence intervals.

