### Interim analyses {21b}

We will perform a blinded sample size re-estimation after the second influenza season. The objective will not be to evaluate the treatment effect, but to check the basis of our sample size calculation (median time to clinical improvement and prevalence of patients with symptoms evolving for less than 72 h). No other interim analysis is planned.

Early termination of the trial: Decision about early trial termination is the responsibility of the Safety Monitoring Board (SMB). If any safety signals suggest that withholding antiviral treatment could endanger participants, or if new research findings (from randomized, placebo-controlled trials in hospitalized adults) demonstrate the benefits of antiviral therapy in this population, the SMB will determine whether early termination of the study is necessary.

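### The stated powers (93% overall, 80% in the <72 h subgroup) make no allowance for deaths, although the plan keeps patients who die unimproved in the risk set until day 30

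*Protocol article*

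**What the plan says.** Sample size {14} assumes "median times to clinical improvement of 5.5 days in the placebo group and 4 days in the baloxavir group", which "correspond to a hazard ratio of 1.375" under constant, proportional hazards with 30 days of follow-up, each calculation "at a two-sided significance level of 0.05". It gives 432 patients for at least 90% power overall and 161 per arm for 80% in the <72 h subgroup. Because two thirds of patients are expected to fall in that subgroup, the total is set at 484, and "With that sample size, the study will reach a power of 93% in the general population of hospitalized patients". No proportion of deaths or never-improvers enters the calculation.

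Two later sections fix how deaths enter the primary analysis. Plans to promote participant retention {18b} says of deceased patients that "clinical improvement will be considered as having never occurred until the end of follow-up: those patients will be right censored at 30 days". The estimand text (Definition of relevant intercurrent events) treats death before improvement as failure to improve: "In this case, the time to improvement will be right censored at day 30". Outcome collection {18a} adds that death does not count as discharge.

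Interim analyses {21b} plans a blinded re-estimation after the second season "to check the basis of our sample size calculation", naming the median time to improvement and the <72 h share. The monitoring committee section {21a} repeats those two quantities. It also puts mortality before the committee each season as safety data.

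**The concern.** The power model and the analysis rule describe different data. Under the model everyone improves eventually, and the ratio of improvement hazards stays at 1.375. Under the rule, anyone who dies unimproved remains at risk to day 30 without ever having an event. As other patients improve and leave, these patients become a growing share of the late risk sets. They do so sooner in the arm that improves faster. If mortality is the same in both arms, the hazard ratio therefore drifts towards 1 and then below it, and the Cox estimate is diluted.

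The plan foresees deaths: day-90 mortality and in-hospital clinical failure (which includes death) are secondary outcomes, and the analysis of length of stay allows for the number of deceased patients. The <72 h subgroup matters most, because it is a co-primary objective, it determines the total of 484, and it is sized at 80% with little margin.

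**Working it through.** **Inputs.** From {14}: medians 5.5 and 4 days, HR 1.375, 30 days, two-sided 0.05, N = 484 overall and 322 in the subgroup. From {8}: 1:1 allocation. From {18b} and the estimand text: deaths censored at day 30. Assumed, because the documents give no figure: the proportion d dying before improvement.

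**1. The plan's own figures.**
- Rates are λ = ln 2 / median: 0.1260 per day (placebo) and 0.1733 per day (baloxavir).
- Improved by day 30, 1 − exp(−30λ): 0.977 and 0.994, mean 0.986.
- Expected events: 484 × 0.9858 = 477 and 322 × 0.9858 = 317.
- Freedman power is Φ(√events × (HR − 1)/(HR + 1) − 1.960). Overall: √477.1 × 0.375/2.375 − 1.960 = 1.489, power 93.2%. Subgroup: √317.4 × 0.375/2.375 − 1.960 = 0.853, power 80.3%.
- Schoenfeld, Φ(½ × √events × ln HR − 1.960), gives 93.6% and 81.0%.
- Freedman at N = 432 gives 90.3%. Also 322 × 3/2 = 483, against 484 stated.

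The stated figures reproduce, with no deaths in the model.

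**2. What the day-30 rule does to the hazard ratio.** If a proportion d of each arm never improves and the rest have exponential times, the improvement hazard in arm g is

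h_g(t) = (1 − d) λ_g exp(−λ_g t) / [d + (1 − d) exp(−λ_g t)].

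At d = 3% the ratio baloxavir/placebo is 1.375 at day 0, 1.30 at day 10, 1.17 at day 15 and 0.96 at day 20. It crosses 1 at about day 24, 21 and 19 for d = 1%, 2% and 3%.

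**3. Power under the rule.** These are simulations of the unadjusted log-rank (Cox score) test. Survivors have exponential times with medians 5.5 and 4 days, and deaths are held in the risk set to day 30. Independent runs agree to within about 1 to 2 points.

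| Deaths before improvement, placebo / baloxavir | Overall, N = 484 | <72 h, N = 322 |
|---|---|---|
| 0% / 0% | 93% | 80% |
| 1% / 1% | 89% | 74% |
| 2% / 2% | 84% | 68% |
| 3% / 3% | 80% | 62% |
| 5% / 5% | 71% | 54% |
| 3% / 2.4% | 87% | 71% |
| 3% / 2% | 91% | 76–77% |
| 3% / 1.5% | 94% | 82% |

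With equal mortality, the average hazard ratio falls from 1.38 to about 1.35, 1.32 and 1.30 at 1%, 2% and 3%.

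**4. Source of the loss.** Losing 3% of the events at an unchanged HR would take Schoenfeld power only from 93.6% to 92.9% overall, and from 81.0% to 79.8% in the subgroup. Nearly all of the loss comes from never-improvers staying in the late risk sets.

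**5. Sensitivity at 3% equal deaths.** Defining the medians over all patients, deaths included, gives 79/62. Weibull shapes 0.7 and 1.3 give 85/69 and 75/58.

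**The case against.** A reader might infer that {14} contains an arithmetic error, or that its powers hold only if nobody dies. The documents support neither. The arithmetic is right on its stated inputs. Under the composite strategy, proportional hazards could also be meant for the improvement curve that already includes deaths. That model leaves 2.3% (placebo) and 0.6% (baloxavir) unimproved at day 30, and deaths could sit inside those fractions at full stated power. Equal mortality is also the harsher premise. Preventing serious complications is a stated objective, and a one-third reduction in deaths before improvement restores most of the power.

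The death rate is unknown. The background's "several thousands of patients require hospitalization due to complicated influenza, with hundreds of deaths" is national and gives no rate for this population. The trial excludes patients needing ICU care, high-flow oxygen or non-invasive ventilation, and immunosuppressed patients. Only deaths before improvement or discharge count, and transfer to another hospital counts as discharge. At 1%, overall power is still about 89%. The planned adjustment for age, vaccination, baseline NEWS2, BMI and site may recover some power, by an amount the documents do not allow to be estimated.

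It is also tempting to say that the season-2 review would be blind to the problem. That goes too far, because {21a} already puts mortality before a committee that includes a statistician.

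All of this limits the size and certainty of the loss. It does not remove the gap: {14} states no assumption about deaths, and mortality is not listed as an input to the re-estimation.

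**Conclusion.** The concern holds in a limited form. The 93% and 80% come from a model that omits the plan's own rule for deaths. If deaths before improvement are 1% to 3% and equal in both arms, the cost against the stated figures is about 4 to 13 points overall (93 to 89–80) and 6 to 18 points in the <72 h subgroup (80 to 74–62). The loss is smaller with a modest mortality benefit and nil if mortality is halved. These sizes rest on assumed death rates, exponential times among survivors and an unadjusted test.

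The documents do not show that the trial is underpowered, only that its stated powers depend on an unstated assumption to which they are sensitive. Severity is moderate: a planning figure and a monitoring input need correction, while the endpoint and the primary analysis are untouched.

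**What to change.** - In {14}, state an assumed proportion dying before improvement in each arm. Restate both powers under the day-30 rule over a range such as 1% to 5%, once with equal mortality and once with reduced mortality on baloxavir. If proportional hazards are meant for the curve that includes deaths, say so.
- In {21b} and {21a}, add the pooled, blinded proportion dead or unimproved at day 30 to the median and the <72 h share as inputs to the season-2 re-estimation.

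The cost is a less favourable stated power and one more pooled quantity, which needs no unblinding. No change in enrolment is part of this fix.
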